#### Qualitative data management:

At each study site, coinvestigators supervised the process of data collection. All audios, interviews, and summaries were coded and saved in the local team’s servers. All data will be shared with Yale University and Emory University team members through a secure online data sharing and storage platform. Only trained team members will be able to access the documents on this platform. At all sites, all focus group discussions and cognitive interviews were audio-recorded, and all texts or audio captured were transcribed in preferred local languages and then translated into English verbatim. The languages used at each site were as follows: Portuguese in Mozambique; Spanish in Guatemala; Tamil in India, and Urdu and Sindhi in Pakistan. Transcripts and field notes were anonymized through the redaction of identifying details prior to translation. Digital recordings of FGDs and cognitive interviews were destroyed after transcription; therefore, only the researchers conducting the FGDs, and cognitive interviews and the transcriber had access to unredacted data. All quotations or descriptions used in reports were anonymized, and additional potentially identifying details will be redacted or altered to further protect anonymity. All photographs and video footage were only taken with consent and would be appropriately anonymized. To ensure privacy, participants were requested to choose between the actual name or nickname for the contact person or location. All signed consent forms were stored by the data manager in a locked cabinet in the office.

### Quantitative Phase

The goal of the quantitative phase is to collect and summarize data on the rates and characteristics of social contacts using social contact diaries and electronic proximity sensors. Quantitative data collection was scheduled in phases across the sites over two years.

#### Contact diary study

*Sample size*: Our study sample will be divided into 10 age groups (<6 months, 6–11 months, 1–4 years, 5–9 years, 10–14 years, 15–19 years, 20–29 years, 30–39 years, 40–59 years, and 60+ years). We framed our sample size calculations to detect sufficient precision in infants <6 months old, an age group of high interest. We powered each age group to have a standard deviation consistent with the precision in the estimate of the youngest age group (0–4 years) in the POLYMOD study (standard deviation = 7.65 contacts per day) (31). We chose to base our sample size calculation on the youngest age group because infants less than six months of age represent the smallest fraction of the overall population size and whose data are largely unavailable since they require a literate older person to keep records on their behalf (19). We inflated the sample size by 10% for each age group to account for attrition due to study withdrawal and loss to follow-up. This resulted in a sample size of 63 per age group per site, thus 630 for each site, 1260 per country, and 5040 participants overall.

#### Electronic proximity sensor study

*Sample size*: We will recruit 63 households per site (126 per country). At each site, households with a child aged <6 months, 6–11 months, 1–4-years were selected randomly and proportional to these age groups.

##### Participant selection:

Once we locate a household, we will make an initial visit (visit 1) to seek permission from the head of the household to allow us to engage the other household members. In Guatemala only, where we do not have sampling frame, we identified household clusters around a 200 m^2^ radius using satellite imagery from Bing. From a central location in each cluster, we approached all households in sequence until we attained our target sample size. We will obtain written informed consent (adults ≥18 years old) or assent (for children aged <18 years).

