#### Quantitative data analysis

##### Construction of age-specific contact matrices.

The primary outcome from this analysis will be age-specific contact matrices containing the average (or expected) number of contacts made per day between age groups combinations. We will create three age-specific contact matrices for each study site: a matrix of physical contacts only, a matrix of nonphysical contacts, and a matrix of all contacts (both physical and nonphysical contacts).

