**Figure 5. F5:**
[figure not shown]
Household contact network. Contact networks will be visualized in order to depict the presence, type and characteristics of contacts (edges). Here, as an example, household members are represented as nodes color coded for relationship to the infant. The thickness of the edges represents cumulative time in contact, with thicker/darker edges representing more time spent in contact.

**Table 1. T1:** Study site characteristics

Country	Mozambique		Guatemala		India		Pakistan	
Study site	Rural	Urban	Rural	Urban	Rural	Urban	Rural	Urban
	Manhiça District, Maputo Province	Bairro Polana Caniço, Maputo City	Concepción Chiquirichapa: Telená, Tuilcanabaj (Centro/Bodega) San Juan Ostuncalco: Monrovia and La Esperanza in the Quezaltenango Department	San Juan Ostuncalco: Centro San Juan. Concepción Chiquirichapa: Centro Concepción	Kilarasampet, Kathalampet in Kaniyambadi Block, Vellore district, Tamil Nadu.	Ward 59, Vellore corporation	Matiari	Ali Akber Shah Goth in Karachi East
Source of participant data	Existing demographic surveillance system (DSS) in Manhiça and Polana Caniço		Randomized sampling from selected households in 57 clusters identified by aerial imaging		Existing DSS		Existing DSS for <5-year-old and 15–49-year-old women in Karachi;	

**Table 2. T2:** Recruitment period for qualitative phase.

Study Sites	Recruitment Start Date	Recruitment End Date

Mozambique	04 August 2020	16 October 2020
Guatemala	19 July 2021	05 November 2021
India	16 February 2022	12 April 2022
Pakistan	14 Dec 2022	18 Feb 2023

**Table 3. T3:** Recruitment period for quantitative phase

Study Site	Recruitment Start Date	Recruitment End Date

Mozambique	05 April 2021	05 April 2022
Guatemala	03 March 2022	22 December 2022
India	25 July 2022	04 February 2023
Pakistan	02 June 2023	Ongoing

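### Guatemala households are reported as randomly selected but were approached in sequence from a central point until a target was met; the Karachi source listed in Table 1 does not cover all ten age groups

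*Protocol article*

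**What the plan says.** **Guatemala.** Three places in the protocol article describe selection.

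- Electronic proximity sensor study, sample size: "At each site, households with a child aged <6 months, 6–11 months, 1–4-years were selected randomly and proportional to these age groups".
- Table 1, row on the source of participant data: "Randomized sampling from selected households in 57 clusters identified by aerial imaging".
- Participant selection: "In Guatemala only, where we do not have sampling frame, we identified household clusters around a 200 m^2^ radius using satellite imagery from Bing", followed by "From a central location in each cluster, we approached all households in sequence until we attained our target sample size".

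**Karachi.** The Pakistan cell of Table 1 reads "Existing DSS for <5-year-old and 15–49-year-old women in Karachi" and ends in a semicolon. No source for Matiari can be read.

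**What the samples are for.** Under Contact diary study, "Our study sample will be divided into 10 age groups", from under 6 months to 60 years and over, with 63 people per group at every site. Under Construction of age-specific contact matrices, "We will create three age-specific contact matrices for each study site".

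**The concern.** A walk from a central point that stops when a target is reached is not a random sample of households. Unless every household in the cluster is reached, those late in the sequence have a lower and unknown chance of entry. If people near the centre of a settlement meet more or fewer others than people at its edge, the estimates shift, and no standard error reveals it. Calling the procedure randomized hides this from modellers who reuse the matrices.

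In Karachi the listed source holds no males aged 5 or over, no children aged 5–14 and nobody aged 60 or over, yet all ten age groups must be filled. If the missing ages are reached through households in that system, a household with neither a child under 5 nor a woman aged 15–49 cannot enter.

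The Introduction criticises earlier studies because differences between populations could not be separated from differences in design. Selection that varies by site, and is not reported as such, brings the same difficulty into the rural–urban and country contrasts.

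**Working it through.** **1. The plan's own totals.** 63 × 10 = 630 per site; 630 × 2 = 1260 per country; 1260 × 4 = 5040. These reproduce. The 63 follows from n = (1.96 × SD / h)² with the stated SD of 7.65 if one assumes 95% confidence and a half-width h of 2 contacts per day, neither of which is stated: (1.96 × 7.65 / 2)² = 56.2, so 57; 57 × 1.10 = 62.7, so 63. The point below does not depend on this figure; it serves only as a yardstick.

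**2. Guatemala: the three descriptions side by side.**

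| Place | Frame | Selection of households |
|---|---|---|
| Sensor study, sample size | not stated | random, at each site |
| Table 1 | 57 clusters from imagery | randomized |
| Participant selection | none | all approached in sequence from a central point until the target is met |

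The first and third rows belong to the same sub-study, so they cannot be explained as two different samples. The third is the only one that says what field staff did.

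**3. The radius.** A radius cannot be in square metres. A circle of 200 m² has radius √(200/π) = 8.0 m. A radius of 200 m encloses π × 200² = 125,664 m², about 628 times as much. With 1260/57 = 22 diary participants per cluster on average (if the diary sample came from these clusters), the 8 m reading is implausible. This is a unit slip, but the sponsor must confirm which unit was meant.

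**4. Size of any bias.** It cannot be computed from the documents. By assumption only: bias = share of people missed × difference in mean contacts. A share of 10–50% and a difference of 1–3 contacts per day give 0.1 to 1.5 contacts per day, against the assumed half-width of 2.

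**5. What clustering does to the intervals.** Assume the Guatemala diary sample is spread evenly over the 57 clusters. Each age group then has 126/57 = 2.2 people per cluster, where 126 = 2 × 63. Design effect = 1 + (m − 1) × ICC; half-width = 1.96 × 7.65 / √(57 / design effect). The intracluster correlation (ICC) is assumed.

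| ICC | Design effect, one age group (m = 2.2) | Half-width | Design effect, all ages pooled (m = 22.1) |
|---|---|---|---|
| 0 | 1.00 | 1.99 | 1.00 |
| 0.01 | 1.01 | 2.00 | 1.21 |
| 0.05 | 1.06 | 2.05 | 2.06 |
| 0.10 | 1.12 | 2.10 | 3.11 |

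The effect is small within an age group. It is larger for analyses that pool ages.

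**6. Karachi: listed source against the ten age groups.**

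- Fully covered (3): under 6 months, 6–11 months, 1–4 years.
- Partly covered (4): 15–19, 20–29 and 30–39, women only; 40–59, women aged 40–49 only.
- Not covered (3): 5–9, 10–14, 60 and over.

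**The case against.** Several points on the other side have force.

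- **Bias is not shown.** A reader might infer that the Guatemala and Karachi matrices are biased. The documents do not support that. The 57 clusters may have been chosen at random, and if a cluster was fully enumerated the walk added no selection within it. The risk stands; its direction and size are unknown.
- **Reach to the diary matrices is inferred.** The Participant selection section sits under the sensor-study heading, and the abstract builds the matrices from diaries. Table 1 describes the source of participants for the study as a whole, which makes the inference reasonable but not certain.
- **Table 1 might mean something narrower.** Its wording could describe a random draw of participants within households already reached. That would ease the conflict with Table 1, but not the conflict with the sensor-study sentence, which concerns households.
- **Karachi can be over-read.** A reader might count the 7 age groups covered partly or not at all and conclude that 7 × 63 = 441 of 630 participants (70%) fall outside the frame. That treats the surveillance system as a list of persons and pools partial with absent coverage. If it serves as a list of households, the excluded group is households with no child under 5 and no woman aged 15–49, and the documents do not give their share. The table cell also looks cut off.
- **The statement that only Guatemala lacks a frame** may be correct for the sensor study, which needs households with a child under 5. The documents do not show it to be false.

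**Conclusion.** The contradiction on Guatemala holds. The article claims random household selection in two places and describes sequential selection without a frame in the third. Unless a random step can be documented, the claim should go, and Guatemala estimates should be presented as at risk of selection bias. Under-representation of outlying households follows only where the target was met before a cluster was exhausted, which the article does not state. Application to the diary matrices rests on reading Table 1 as covering the whole study.

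For Karachi, the mismatch between the listed source and ten all-age groups is real: 3 covered, 4 partly, 3 not. It supports a stated limit on coverage. It does not support a numerical claim about how much of the population is missed, nor any conclusion about Matiari.

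**What to change.** **Guatemala (recruitment closed on 22 December 2022 according to Table 3).**

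1. Reconcile the sensor-study sample-size paragraph, Participant selection and Table 1 to sequential (quota) sampling within 57 image-identified clusters. State any random step that was actually used, including how the clusters were chosen.
2. Correct the radius to the intended unit.
3. Compute Guatemala intervals with cluster-robust or cluster-bootstrap methods. The cost is somewhat wider intervals. This does not remove selection bias; it makes the stated precision honest.
4. Where household location is held, compare contact counts with distance from the cluster centre and report the result.

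**Karachi (Table 3 lists Pakistan recruitment as ongoing).** State how people outside the listed groups are found. If they are reached through households in the surveillance system, define the Karachi target population as households with a child under 5 or a woman aged 15–49, and qualify the rural–urban and country contrasts accordingly. Do not change the frame now: a new listing would need extra fieldwork and would put two sampling methods into one site.

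The cost is mainly wording, one change of variance method and one descriptive check. No new data are needed.

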##### Study procedures:

To train all the participants in diary-keeping and sensor-wearing procedures, we will request the head of the household to select a day of the week when all household members will be present at the same time. On this selected day (start day), we will visit the household and train the members on the diary and sensor study procedures (figures 3 and 4). Each participant will wear the sensor over 7 continuous days for data collection. Participants will be required to doff the sensor when not in use such as when sleeping or leaving the house, or when encountering water. In addition, the head of the household will select one day at random (diary day one) between the start day and end day (7 days after start day). Each household member will be required to keep a record of their contacts in the paper diary on two consecutive days. The research team will record the date and time when the sensors were issued and collected, while participants will keep a daily log of when the sensors were worn or taken off. Data from each sensor will be individually downloaded into a laptop at the site office.

#### Quantitative data analysis

##### Construction of age-specific contact matrices.

The primary outcome from this analysis will be age-specific contact matrices containing the average (or expected) number of contacts made per day between age groups combinations. We will create three age-specific contact matrices for each study site: a matrix of physical contacts only, a matrix of nonphysical contacts, and a matrix of all contacts (both physical and nonphysical contacts).

##### Identifying predictors of number and duration of contacts.

We will investigate whether certain demographic and biologic characteristics are predictors of the frequency and nature of contacts. This regression analysis will result in the identification of key drivers of contact.

##### Defining contacts using wearable sensors.

To comprehensively profile the frequency, duration and intensity of social contacts of young infants with their household members, we will analyze high resolution data collected using wearable proximity sensing devices. Data collected from each participant will be obtained and cleaned separately. In sensitivity analyses, different time-interval definitions of a ‘contact’ will be considered.

##### Validation of diary-based collection (Sensor Study).

We will use the sensor data to validate the diary data using two methods. First, using variables that characterize each contact such as age, sex, duration, and relationship, we will identify contacts that were identified by [1] diary, [2] sensor, or [3] both. We will then calculate the level of agreement between diary and sensor data using Cohen’s kappa coefficient (k). Second, using sensor data, we will construct age-specific contact matrices containing the average number of contacts made per day using the methods described in the contact diary study. We will compare these matrices with those generated from diary data but restricted to household contacts using the coefficient of accuracy (C(a) and the coefficient of determination (r_c_). C(a) measures the accuracy and r_c_ measures the precision of the relationship between the two data collection methods (32). We will then perform the same comparisons for data on the duration of contacts.

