#### Wearable proximity sensors.

We purchased an open-source off-the-shelf proximity sensor that was manufactured in the US, satisfies Federal Communications Commission (FCC) regulations, is relatively cheap, customizable, and small enough to be carried by people of all ages (figure 2). We selected the Adafruit Feather nRF52840 Sense sensor [https://learn.adafruit.com/adafruit-feather-sense] that uses active unidirectional Bluetooth Low Energy operating at 2.4 GHz to periodically transmit and receive data packets over short ranges relevant for respiratory infection spread.(25) It measures 51 mm × 23 mm × 7.2 mm and weighs approximately 6 grams. It has an on-board memory chip for data storage and is powered by a 3.7 V 500 mAh. We redesigned and updated the firmware used in the SocioPatterns project [www.sociopatterns.org] to be compatible with our new sensors. We also designed and 3D-printed tamper-proof, weather-proof plastic cases to enclose the sensor and battery. A fully assembled sensor with a battery and plastic case has a total cost of ~$40 and weighs ~20–30 grams. Prior to deployment, we conducted rigorous testing on case design, utility (ensuring radio communication between sensor dyads is achieved), signal propagation (how far signals are propagated, effects of multipath on signal strength), durability of battery charge and storage space capabilities (to establish optimum experiment duration). When in proximity, sensor dyads exchange data packets consisting of the sensor identifier (ID), timestamp, and transmission power level (received signal strength indicator, RSSI). Similar to previous studies, a ‘contact’ was defined as occurring between two individuals if their sensors exchanged at least one data packet over a 20-second interval. After a contact is established, its duration is defined as the interval in which the devices continue to exchange at least one packet for every subsequent 20s interval. Conversely, a contact is defined as broken if a 20-s interval lapses with no exchange of radio packets.(26) When worn on the chest area, signal exchange occurs when individuals are face-to-face within 1–1.5 meters of each other, thus defining proximity that may be relevant for transmission of respiratory infections. Assuming 8 hours of continuous data collection per day, the onboard sensor memory can log data packets for up to 7 days. It is stressed that the sensors detect face-to-face proximity between individuals by assessing the attenuation of the signals with distance but not an actual physical touch. Previous sensor deployment suggested that a 20-second interaction can be considered as a reasonable duration to describe “the fastest social interactions”, such as a quick conversation or handshake in a social gathering that may lead to the transmission of respiratory infections through droplets from coughing or sneezing.(26)

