Despite the use of rigorous mixed qualitative and quantitative methods, we anticipate some challenges. Participants may only recall contacts that are recent or salient (those that are most important, such as meeting family or friends compared to strangers). This may lead to an underestimation of contact rates. We expect that children who are not in school and those aged less than 10 years old may not be able to self-report their contacts. Additionally, adults who are unable to or have limited ability to read and write may not be able to record their contacts in the paper contact diaries. For these groups, we will assign parents/guardians as “shadows” to the children to help with recording contacts. Then adult participants will be asked to select an individual to record their contacts on their behalf. This would require adequate training of both participants and shadows to understand diary keeping procedures while respecting the privacy of the participants. Furthermore, to profile the social contacts of infants with their household members using contact diaries and wearable proximity sensors, only interactions between participants wearing sensors will be recorded. Sensors do not record touch or other characteristics of interactions between participants. Therefore, while the sensors provide accurate and time-resolved data on physical proximity, they lack the richness of the characteristics of the contact. The site-specific contact matrices and all underlying data will be made publicly available. Study findings will be published in scientific journals and presented at national and international scientific and programmatic forums.

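### The diary–sensor kappa is planned on recorded contacts only, with no 'neither' cell, so as written it cannot be positive

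*Protocol article*

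**What the plan says.** The section on validation of diary-based collection gives two methods. In the first, "using variables that characterize each contact such as age, sex, duration, and relationship", the plan says "we will identify contacts that were identified by [1] diary, [2] sensor, or [3] both". The next step is to "calculate the level of agreement between diary and sensor data using" Cohen's kappa. The second method builds contact matrices from the sensor data and compares them with diary matrices limited to household contacts, using a coefficient of accuracy and a coefficient of determination. Contact duration is then compared in the same way.

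Other sections bear on the first method:

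- **Wearable proximity sensors:** two people are in contact "if their sensors exchanged at least one data packet over a 20-second interval".
- **Study procedures (sensor study):** "Each household member will be required to keep a record of their contacts in the paper diary on two consecutive days". Sensors come off for sleep, near water and on leaving the house. Participants log when the sensor is on or off.
- **Discussion:** "only interactions between participants wearing sensors will be recorded".
- **Enrollment survey:** household size and composition are collected.
- **Contact diary:** the listed fields for a contact are age, sex, relationship, location, frequency and duration. A participant identifier is not among them.

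**The concern.** Kappa for diary yes/no against sensor yes/no needs four cells, including the units that both methods call negative. Here the unit is a recorded contact. A diary contact exists only if it is written down, and a sensor contact only if a packet was exchanged. A pair that did not meet leaves no record in either source, so the classification as described has three cells.

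The wording also places no household limit on the first method. A diary contact with someone who wears no sensor, or one made while the sensor was off, can therefore be counted as missed by the sensor.

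The contact matrices are the primary outcome and are to be released for modelling. A kappa at or below zero would suggest that the diaries behind them are unreliable, even if the two methods largely agree. If a denominator is supplied only during analysis, the value of kappa will depend on a choice made after the data are in.

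**Working it through.** The article states no kappa value, target or sample size for kappa, so there is no figure to reproduce. The counts below are illustrations.

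**Notation.** a = both, b = diary only, c = sensor only, d = neither, n = a + b + c + d.

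**General formula.** kappa = 2(ad − bc) / [(a+b)(b+d) + (a+c)(c+d)].

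**As written (d = 0).** kappa = −2bc / [b(a+b) + c(a+c)]. The numerator is never positive. If b and c are both above zero, kappa is negative. If only one of them is zero, kappa is exactly 0. If both are zero, it is 0/0. A grid over a = 0–200 and b, c = 0–40 gave a maximum of 0.

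| a / b / c | kappa with d = 0 | positive agreement 2a/(2a+b+c) |
|---|---|---|
| 80 / 10 / 10 | −200/(900 + 900) = −0.11 | 160/180 = 0.89 |
| 95 / 3 / 2 | −12/(294 + 194) = −0.02 | 190/195 = 0.97 |
| 98 / 1 / 1 | −2/(99 + 99) = −0.01 | 196/198 = 0.99 |
| 90 / 10 / 0 | 0/(1000 + 0) = 0 | 180/190 = 0.95 |

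**With a 'neither' cell.** The documents do not give d, so a range is shown for 80/10/10:

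- d = 5: 2(400 − 100)/(2 × 90 × 15) = 600/2700 = 0.22
- d = 20: 2(1600 − 100)/(2 × 90 × 30) = 3000/5400 = 0.56
- d = 100: 2(8000 − 100)/(2 × 90 × 110) = 15800/19800 = 0.80

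**On the study's scale.** The article says "We will recruit 63 households per site (126 per country") and asks for two diary days. Assume 5 members per household, a figure not in the article. That gives 10 pairs × 2 days × 63 households = 1260 pair-days per site. If the detected contacts split 80/10/10 per cent, kappa is 0.23, 0.42, 0.60 and 0.76 when 5%, 10%, 20% and 40% of pair-days are 'neither'.

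**Household restriction.** Diary contacts that no sensor could have recorded add only to b. That lowers positive agreement 2a/(2a+b+c), but leaves a/(a+c), the share of sensor contacts also in the diary, unchanged. With d = 0, kappa stays at or below zero whatever is added.

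**The case against.** The strongest reply is that the article omits the 'neither' cell without excluding it. Households are closed groups, their composition is recorded, and the contact-network section already plans a household adjacency matrix, a structure that holds pairs without contact. A condensed article may leave the table layout to the full plan. This shows that a denominator is available and the repair is cheap. It does not put a denominator into the stated analysis: the article names both the classification and the statistic, and nothing ties the roster or the adjacency matrix to kappa.

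Kappa might instead be meant for the attributes of matched contacts. The attributes listed are those used to identify the contacts, so agreement on them would be largely built in.

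On the household restriction, it is fair to say that the section concerns the sensor study and that relationship is a matching variable, so the authors may intend household contacts only. A reader might infer a plan to count every community contact as a sensor miss. The text does not say that. It only fails to prevent it.

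A reader might also infer that matching on duration makes the later duration comparison circular. The article does not support this. That comparison follows directly on the matrix comparison and most naturally repeats it, and matrices built separately from each source involve no matched contacts.

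**Conclusion.** The point holds for the first validation method. Followed as written, kappa cannot be positive. It is zero or negative when any contact is discordant (−0.11 for 80/10/10) and undefined when none is, so it carries no useful information about agreement. This follows from the algebra and needs no assumption about the data beyond an empty 'neither' cell. The missing household and wearing-time restriction is a second, smaller gap in the wording.

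It would go too far to say that the whole diary validation fails: the matrix comparison and its duration part stand. Nor can one say what kappa would be after repair. The 0.80 above rests on an assumed 100 'neither' pair-days, and 5 give only 0.22. If most household pairs meet every day, a correctly built kappa could still be low despite good agreement.

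**What to change.** For the first method:

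1. Restrict the comparison to pairs of enrolled, sensor-wearing members of the same household, on diary days and within logged wearing time.
2. Make the unit the household pair-day. Cross-classify diary yes/no by sensor yes/no, with 'neither' taken from the household roster.
3. State how diary entries are matched to roster members. Relationship, age and sex may be needed, because the listed diary fields include no participant identifier. Do not match on duration.
4. Report kappa together with positive agreement 2a/(2a+b+c) and the proportion of sensor contacts also in the diary, a/(a+c), with intervals that allow for household clustering. Alternatively, drop kappa and report those two measures, which need no 'neither' count.

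Fix the denominator before the analysis. The cost is analysis wording and code, plus some work matching diary entries to the roster. The article already plans to collect household composition, two diary days and wearing logs, so no new data collection is foreseen. The second method needs no change.

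### Cohen's kappa computed on contacts seen by diary, sensor or both has an empty 'neither' cell, so as written it can never be positive

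*Protocol article*

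**What the plan says.** The section on validation of diary-based collection (Sensor Study) states: "We will use the sensor data to validate the diary data using two methods". The first method works contact by contact. Using age, sex, duration and relationship, "we will identify contacts that were identified by [1] diary, [2] sensor, or [3] both". The next sentence reads "We will then calculate the level of agreement between diary and sensor data using" Cohen's kappa. The second method compares sensor-based and diary-based household contact matrices by the coefficient of accuracy C(a) and by r_c, and then repeats the comparison for duration.

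The three groups are numbered and none of them is 'neither'. The section defines no set of possible pairs, or of pairs per day, from which joint absences could be counted.

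Both tools produce only positive records. Under Wearable proximity sensors, two people are in contact "if their sensors exchanged at least one data packet over a 20-second interval"; if no packet passes, no contact is logged. Under Study procedures of the sensor study, "Each household member will be required to keep a record of their contacts in the paper diary on two consecutive days"; the diary lists contacts that were made.

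**The concern.** Kappa compares observed agreement with the agreement expected by chance, and agreement has two parts: both tools say yes, or both say no. If the analysis set is the list of contacts that at least one tool detected, the second part is empty by construction. Chance agreement computed from the margins is then at least as large as observed agreement, so kappa cannot rise above zero however well the diary performs.

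This matters because the article itself expects recall error and under-reporting in diaries, and kappa is the only agreement coefficient it names for whether the same contacts were captured. A team that followed the text could report a kappa slightly below zero for a diary that matches the sensor on nearly every contact. The stated classification and the stated statistic do not fit together, and an analysis plan that followed the text faithfully would inherit the problem.

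**Working it through.** **Inputs.** The three groups and the statistic come from the validation section. The article gives no counts and no target value for kappa, so there is no stated figure to reproduce. All counts below are assumptions chosen for illustration.

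**Notation.** a = both, b = diary only, c = sensor only, d = neither, n = a + b + c + d.

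- Observed agreement: po = (a + d)/n
- Chance agreement: pe = [(a+b)(a+c) + (c+d)(b+d)]/n²
- kappa = (po - pe)/(1 - pe)

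**With d = 0**, n = a + b + c, and

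po - pe = [a(a+b+c) - (a+b)(a+c) - bc]/n² = -2bc/n²

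kappa = -2bc/[n² - (a+b)(a+c) - bc]

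The numerator is zero or negative. The denominator equals b(a+b) + c(a+c), which is positive unless b = c = 0. In that case pe = 1 and kappa is 0/0.

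**Example.** 90/5/5: -2 × 25/[10000 - 95 × 95 - 25] = -50/950 = -0.053.

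| both / diary only / sensor only | po | kappa | positive agreement 2a/(2a+b+c) |
|---|---|---|---|
| 98/1/1 | 0.98 | -0.010 | 0.99 |
| 90/5/5 | 0.90 | -0.053 | 0.95 |
| 90/10/0 | 0.90 | 0.000 | 0.95 |
| 80/10/10 | 0.80 | -0.111 | 0.89 |
| 70/10/20 | 0.70 | -0.154 | 0.82 |
| 50/25/25 | 0.50 | -0.333 | 0.67 |
| 100/0/0 | 1.00 | undefined | 1.00 |

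Over every table with n = 100 and d = 0, the largest kappa found was 0.

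**With a 'neither' cell**, kappa = 2(ad - bc)/[(a+b)(b+d) + (a+c)(c+d)]. For 90/5/5 with d = 5: 2(450 - 25)/[95 × 10 + 95 × 10] = 850/1900 = 0.45.

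| assumed d | kappa, 90/5/5 | kappa, 80/10/10 |
|---|---|---|
| 5 | 0.45 | 0.22 |
| 10 | 0.61 | 0.39 |
| 20 | 0.75 | 0.56 |
| 50 | 0.86 | 0.72 |
| 100 | 0.90 | 0.80 |

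**How many pair-days there would be.** The article plans 63 sensor households per site and two diary days. If a household has H sensor-wearing members (H is assumed), a site yields 63 × 2 × H(H-1)/2 pair-days: 756 for H = 4 and 3528 for H = 8. The article does not say how many of these would be free of contact by both tools.

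**The case against.** The strongest reply is that the degenerate table is inferred. The text sorts contacts and then speaks of agreement between diary and sensor data; it does not say that the three groups are the whole kappa table, and it does not exclude pairs without contact. All household members are trained to wear sensors and keep diaries, so a closed set of pairs exists, and the section on the aggregated contact network defines an adjacency matrix in which absent edges can be counted. A condensed article may also leave the unit of analysis to a fuller document.

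Part of this stands: a 'neither' cell could be built, and nothing forbids it. But the validation section does not build one. The adjacency matrix belongs to a separate network analysis, aggregated over the whole study period rather than by diary day. Nor can kappa be read as agreement on attributes such as duration, because those variables are used there to identify contacts, not as the ratings compared. Even on the generous reading kappa stays undetermined until the set of pairs is fixed, as the second table shows.

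A reader might infer three stronger things that the documents do not support:

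- *That the whole diary validation fails.* It does not. The three-way counts are contact-level information in their own right, and the C(a), r_c and duration comparisons do not use this table.
- *That kappa would be unrelated to agreement.* With b = c it falls steadily from -0.01 to -0.33 as overlap falls from 98 to 50 per 100. It varies with agreement but stays at or below zero.
- *That a full table would show kappa near 0.90.* That figure needs 100 'neither' pairs beside 90/5/5. If nearly all household pairs meet daily, d is small and kappa much lower.

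**Conclusion.** The point holds for the procedure as written. Classifying only detected contacts and then computing kappa gives a statistic that is zero or negative for every possible table, or undefined at perfect agreement, so it is uninformative as a measure of diary validity. This part is algebra and rests on one reading: that the three listed groups make up the table. The example values rest on assumed counts.

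The consequence is limited. The primary outcome is the set of age-specific contact matrices, diary validation is not one of the three aims listed in Materials and Methods, and no sample size depends on kappa. The paragraph should be corrected before the validation is analysed. The data collection and the main results are not called into question.

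**What to change.** Reword the first validation method.

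1. **Main contact-level results.** Report positive agreement 2a/(2a+b+c), the share of sensor-detected contacts recorded in the diary, a/(a+c), and the share of diary-recorded household contacts detected by the sensor, a/(a+b). None of these needs a 'neither' cell.
2. **Kappa, if kept, as secondary.** Take as the unit every pair of sensor-wearing members of a household on each diary day. Pairs with no contact by either tool then fill the fourth cell. Show the full table beside kappa, because its value depends strongly on that cell.
3. **Restriction.** Limit diary contacts to household members and to time when both sensors were worn according to the wear logs. Study procedures has sensors taken off for sleep, water and leaving the house; without the restriction, contacts during non-wear would count as sensor misses. The listed diary items do not include clock time, so the restriction may have to be applied approximately, for example by location and by amount of joint wear that day.
4. **Matching.** Use the name or nickname of the contact where recorded, otherwise age, sex and relationship as the section already plans. The Contact diary section lists no household roster identifier, so one should not be assumed.
5. **Precision.** Use intervals that allow for clustering by household.

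The cost is one rewritten paragraph and a little more analysis work on data already planned. The downsides are some matching error and an unstable kappa if nearly all pairs meet every day, which is why kappa should not be the main result.
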